### Interventions

Participants in the control group will receive ‘The Back Book’ educational booklet (Additional file 1) which contains written information about techniques for dealing with back pain. It has been demonstrated that this booklet has no significant effect on improving pain or function in people with chronic nonspecific LBP [31].

The intervention group will also receive ‘The Back Book’. In addition, they will be issued a pair of Formthotics™ prefabricated foot orthoses (Foot Science International Ltd., Christchurch, New Zealand, Fig. 2). The prefabricated foot orthoses will be heat moulded to fit the participant’s feet as per the manufacturer’s instructions. The devices will be worn in the participant’s usual footwear for 1 year from baseline. Wearing in instructions will be provided by the therapist (registered podiatrist), issuing the intervention. During the fitting process participants are shown, by the therapist, how the devices are fitted to their footwear. Participants are instructed to wear the devices as much as possible and that they may change them to other suitable shoes. Shoe suitability will be discussed as part of the fitting process. Participants in the prefabricated orthotic group will be provided with a usage diary. This and each intervention will be provided to participants by the therapist who is located in a separate room, after baseline questionnaires and clinical measurements are completed.

**Fig. 2 Fig2:**
[figure not shown]
Example of prefabricated orthoses

### Data collection sessions

Participants will be required to attend two data collection sessions: baseline and 12 weeks later (Fig. 1). Follow-up questionnaires will be mailed to participants at 26 and 52 weeks after the baseline session.

After the GP has screened a participant and they have contacted the researcher for phone screening, a baseline testing session will be arranged, and they will be sent a general health questionnaire which they will be asked to bring completed to the baseline testing session. The general health questionnaire consists of questions about sociodemographic variables. During the phone screening, potential participants will be asked about current and previous treatments for their LBP and instructed to wear suitable attire for clinical testing and to bring multiple pairs of lace-up or Velcro, enclosed footwear.

The assessor ([name]), who will be blinded to treatment allocation, will conduct baseline and follow-up anthropometric and clinical measurements, and issue self-administered baseline and follow-up questionnaires to participants.

#### Anthropometric measurements

Weight will be measured using standard bathroom scales. Waist circumference will be measured using a tape measure. Height will be measured with a wall-mounted tape measure.

#### Clinical measurements

To avoid an order effect, the order of the clinical measurements for each participant will be randomised using an online random sequence generator. For measures that have multiple components, such as gluteus medius muscle activity and transversus abdominis muscle thickness (Table 1), the order of these individual components will also be randomised. For any clinical measurement conducted at subsequent sessions, the order will be the same as at baseline. The left and right side will be tested for each clinical measurement, except for the gluteus medius and transversus abdominis measurements where only the right side will be measured (Table 1). To comply with the assumption of independence of data, when the left and right sides are measured, both sides will be combined to obtained an average [51]. When both sides are measured (e.g. range of motion), two measurements will be taken per side. All clinical measurements will be taken at baseline with only the gluteus medius muscle activity and transverses abdominis muscle thickness remeasured at the 12 week follow-up.

**Table 1 Tab1:** Overview of clinical measurements

Clinical measurement	Technique
Weight bearing ankle joint dorsiflexion ROM (knee flexed) [32]	• Participant stands facing the wall and places two hands on the wall shoulder-width apart. The leg being tested is positioned perpendicular to the wall and they extend their ipsilateral hip. • Participant then performs the lunge, dorsiflexing their ankle to its maximum end-point with the participant’s knee flexed. • The foot must remain perpendicular to the wall and their calcaneus must remain on the ground. • The digital inclinometer is then placed on the anterior aspect of their tibia, approximately 15 cm distal to the tibial tuberosity and the angle recorded.
Weight bearing ankle joint dorsiflexion ROM (knee extended) [33]	• As described above but with the knee extended.
Hamstring ROM [34]	• Participant is supine with the hip and ipsilateral knee flexed to 90 degrees. • Assessor extends the knee with the inclinometer, attached to the neoprene material, on the anterior tibia until the end ROM.
Internal and external hip ROM (hip flexed to 90 degrees) [35]	• Participant is positioned in a supine position with their hip and knee at 90 degrees and their lower legs are hanging over the edge of the examination chair. • Assessor rotates hip through internal ROM, holding the lower leg that has the inclinometer attached to the neoprene material, until the end of internal ROM. The inclinometer is positioned on the distal third of the fibula. • The same is then done for external ROM.
Internal and external hip ROM (hip extended to 180 degrees) [35]	• As described above but the participant is lying on their back so that the hip is at 180 degrees. The knee remains flexed at 90 degrees.
Frontal plane ankle joint ROM [36]	• Participants is seated with their hip and knee at 90 degrees. • The goniometer will be placed on the front of their ankle and top of their foot. The goniometer will be positioned at the midpoint between the malleoli and align with the second digit of the foot being tested. • Participants will be instructed to maximally invert and evert their foot, with the change in angle from the most everted to the most inverted recorded.
Lateral flexion ROM of the lumbar spine [37–39]	• Participant stands upright with a hand on the outside of the ipsilateral thigh. • Participant then laterally flexes so that the hand moves distally on the thigh to the end ROM. • The distance from the starting position of the middle finger to its final position will be measured with a tape measure.
Foot posture index (FPI) [40]	• Participants stand in their normal base of gait and take 6–8 steps on the spot. • The assessor will then grade each foot once against the 6 criteria of the FPI and assign a score.
Glutues medius muscle activity [41–45]	• Using the Delsys Trigno electromyographic device, three side-lying hip abduction maximum voluntary isometric contractions (MVIC) for 5 s, with a 60 s rest between contractions, and resistance applied by the examiner at the ankle, will be conducted • Gluteus medius data will be recorded once barefoot and shod on a hard level surface, at the participant’s self-selected comfortable walking speed, for ten seconds (minimum of five strides).
Transversus abdominismuscle thickness [46–50]	• Using the Shenzhen Mindray M5 ultrasound, three Images will be taken at each of the following: rest, during an active straight leg raise (ASLR) on the right to a height of 20 cm, and an abdominal drawing in manoeuvre (ADIM). • At rest and during the ASLR, the participants will be positioned supine with hips and knees flat on the plinth and arms by their side. A supine hook lying position, with hips flexed to 40–60 degrees and knees flexed to 90–100 degrees, will be used for the ADIM. For the ADIM, participants will be instructed to draw their belly button towards their spine. • Three images will be taken for each position and all will be collected at the end of normal exhalation.

The ROM measures and foot posture index (FPI) will only be measured at baseline and will help to provide an overview of the participants within this trial. To measure range of motion (ROM) a digital inclinometer (Angle Sensor 82201B-00) will be used except for frontal plane ankle joint ROM and lateral flexion of the lumbar spine, which will be measured with a plastic goniometer and tape measure respectively. The digital inclinometer will be adhered to a piece of neoprene that circumducts the lower leg for internal and external hip and hamstring ROM (Fig. 3).

**Fig. 3 Fig3:**
[figure not shown]
**a** Digital inclinometer position for hip internal and external rotation range of motion. **b** Digital inclinometer position for hamstring range of motion

The FPI will be used to assess foot type (Table 1). The FPI consists of six criteria which are graded on a 5 point scale from − 2 to 2, with the score for each criterion summed to create a total score per foot [40]. Foot type will be categorised according to the following: supinated foot (− 1 to − 12), neutral (0 to 5), and pronated (6 to 12) [52].

Skin over the right gluteus medius muscle will be prepared according to the surface electromyography for the non-invasive assessment of muscles (SENIAM) guidelines and a wireless electromyographic sensor (Delsys Trigno™) adhered parallel to the direction of muscle fibres, half way between the line from the iliac crest and the greater trochanter [41]. Foot switches will be used to measure gait events and will be adhered to the planter posterior aspect of the calcaneus, the plantar aspect of the 1st and 5th metatarsal heads, and the plantar surface of the interphalangeal joint of the hallux. Electromyographic measurement of the gluteus medius muscle has been shown to be reliable [42, 53].

Transversus abdominis muscle thickness will be measured with a Shenzhen Mindray M5 diagnostic ultrasound machine and Mindray linear transducer (7L4s), in B-mode at 7.5 MHz, positioned adjacent and perpendicular to the abdominal wall, 25 mm antero-medial to the midpoint between the ribs and ilium, on the mid-axillary line and parallel to the transversus abdominis muscle fibres. Thickness measurements will be made at the hyperechoic fascial lines between the superficial and deep edges of the muscle. Ultrasound measurement of the transversus abdominis muscle has been shown to be reliable [46].

### Follow-up sessions (12, 26 ad 52 weeks)

Participants will be required to return 12 weeks after the baseline testing session to have their gluteus medius muscle activity and transversus abdominis muscle thickness remeasured. Participants will also be required to complete the numeric pain rating scale, Oswestry Disability Index, and International Physical Activity Questionnaire (IPAQ-7). Participants will also be mailed these questionnaires 26 and 52 weeks after baseline testing. At the 12 week follow-up, participants will be asked if they have read ‘The Back Book’. The participant information statements contain the researchers’ contact details so participants can report adverse events at any stage of the trial. Adverse events will be managed by the researchers or participants will be referred to their GP.

### Primary outcomes

The primary outcomes will be change in pain and function from baseline to 12, 26 and 52 weeks. The primary follow-up time point is 12 weeks. It is important to highlight that two primary outcome measures will be used because they are both of clinical importance.

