### Sample size

The sample size for this trial was calculated to find minimal clinically important change of 2 (s = 2.5) on the numeric pain rating scale [29] with 80% power, a 5% Type I error rate and non-adherence rate of 20%. Numeric pain rating scale was chosen for the calculation instead of the Oswestry Disability Index because it had the smaller effect size and thus would require the larger sample size. The calculation adjusted for non-adherence required a total sample size of 30 per group, therefore a total of 60 participants will be recruited.

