This randomised controlled trial will primarily investigate the effectiveness of prefabricated foot orthoses for reducing pain and improving function in people with chronic nonspecific LBP over 52 weeks. Additionally, this study will investigate the effect that prefabricated foot orthoses have on gluteus medius muscle activity and transversus abdominis muscle thickness over 12 weeks, as well as, on the level of physical activity over 52 weeks. The influence that foot type has on the primary outcomes will also be investigated as a secondary outcome. This trial is expected to help inform clinicians and researchers about the effectiveness of prefabricated orthotic devices for the treatment of chronic nonspecific LBP, as well as, help explain their potential mechanism of action in this population.

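### Two primary outcomes, labelled primary at three time points, with no rule for success: 5% is not assured for the primary claim

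*Protocol article*

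**What the plan says.** The Primary outcomes section of the Protocol article opens with "The primary outcomes will be change in pain and function from baseline to 12, 26 and 52 weeks". It continues: "The primary follow-up time point is 12 weeks". The Methods paragraph of the abstract also marks 12 weeks as the primary time point. The reason given for having two primary outcomes is "It is important to highlight that two primary outcome measures will be used because they are both of clinical importance".

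The Secondary outcomes section does not list the treatment comparisons of pain and function at 26 and 52 weeks. Pain and function appear there only through their correlation with foot type.

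The Statistical and data analysis section plans an ANCOVA for each primary outcome at each follow-up point, with the baseline value as the only covariate. It gives no significance level, testing order or division of alpha.

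The Sample size section is the only place with an error rate, "a 5% Type I error rate". It applies to one comparison, a "minimal clinically important change of 2 (s = 2.5) on the numeric pain rating scale". The Oswestry Disability Index (ODI) is mentioned there only to explain why pain drives the calculation.

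The last paragraph of the Discussion states the main aim as effectiveness "for reducing pain and improving function in people with chronic nonspecific LBP over 52 weeks". The Background paragraph of the abstract has the same 52-week horizon.

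**The concern.** Clinical importance is a good reason to measure both outcomes. It does not say what the trial may claim if only one of them shows a difference. Three rules fit the text: either outcome suffices, both are required, or one is tested before the other. They differ in error rate and in power, and the sample size was settled without choosing among them.

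The time points add a second ambiguity. The section names one primary time point but gives the same label to results at all three, and the main aim is framed over 52 weeks. As the text stands, an author could call a function-only result at 12 weeks a primary finding. The label would also give some cover for doing the same with a later result.

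**Working it through.** **Inputs from the Protocol article.** Difference 2 points, SD 2.5 (standardised effect 2/2.5 = 0.8), power 80%, Type I error 5%, allowance 20%, 1:1 allocation, 30 per group.

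**Assumptions.** Tests are two-sided. Sidedness is not stated, but a one-sided test gives 20 per group, or 24 after multiplying by 1.2, and does not reproduce 30. The 5% level is carried over to each primary ANCOVA. The correlation between the pain and function test statistics is not given, so a range of 0 to 0.7 is shown.

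**Step 1: reproduce the plan's figure.**
n per group = 2 × (1.960 + 0.842)² × (2.5/2)² = 2 × 7.85 × 1.5625 = 24.5, rounded up to 25.
25 × 1.2 = 30 per group, 60 in total. This matches the plan. The figure is therefore one two-sided 5% test of pain, with no allowance for a second primary outcome. (Dividing by 0.8 would give 32 per group. That is a separate matter and is not relied on here.)

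**Step 2: either outcome at 12 weeks counts, each tested at 5%.**
P(at least one false positive) = 0.05 + 0.05 − P(both significant when neither effect exists).

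| Correlation | P(both) | P(at least one) |
|---|---|---|
| 0 | 0.0025 | 0.0975 |
| 0.3 | 0.0049 | 0.0951 |
| 0.5 | 0.0093 | 0.0907 |
| 0.7 | 0.0165 | 0.0835 |

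Holding 5% by Bonferroni, at 0.025 each, would need 30 per group before inflation and 30 × 1.2 = 36 after it (72 in total). With all 30 per group, power for pain at 0.025 is 79% to 80% (t and normal calculations). With 30 × 0.8 = 24 per group it is 68% to 70%.

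**Step 3: both outcomes must succeed, each at 5%.**
The chance of a false claim is at most 5%, because a claim requires a false rejection on whichever outcome has no effect. The cost falls on power. Normal approximation, standardised effect of 0.8 assumed on both outcomes, correlation 0 to 0.7:

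| Per group | Pain alone | Both |
|---|---|---|
| 30 | 87% | 76% to 81% |
| 24 | 79% | 63% to 70% |

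The plan says pain has the smaller effect size, so joint power may be somewhat higher than shown. It cannot exceed the power for pain.

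**Step 4: fixed sequence, pain then function, each at 5%.**
If pain has no true effect, any false claim needs a false rejection on pain, so the error is at most 5%. If pain has a true effect, only function can be claimed falsely, again at most 5%. Pain keeps the full 5%, so the calculation in Step 1 stands.

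**The case against.** The strongest reply is that the inflation is conditional. The article never says that either outcome suffices, and it never offers 5% as a trial-wide rate. It states 5% for the pain comparison, where it holds. Co-primary outcomes are a legitimate design, and a both-must-succeed rule keeps 5%. Testing each outcome at 5% is an inference from the Sample size section. This stands, so a reader who infers that the stated 5% is simply wrong goes further than the text allows.

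A reader might also count six primary tests. At 5% each, the chance of at least one false positive would be 1 − 0.95⁶ = 26.5% if they were independent, and about 18% to 25% with correlations of 0.3 to 0.7 between outcomes and between times. The documents do not support this as the size of the problem, because both the abstract and the Primary outcomes section single out 12 weeks. The 52-week phrase can also be read as the span of follow-up. What remains is a labelling inconsistency.

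Finally, a success rule is something that an article may leave to the analysis plan, which is not shown. That answers only part of the point. This article raises the question of two primaries itself, gives a reason that does not bear on error control, fixes a sample size that depends on the answer, and labels the time points inconsistently. A rule in another document would not remove that inconsistency.

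**Conclusion.** The point holds in conditional form. The text leaves open whether one or both outcomes define success, and its only 5% covers one comparison of pain. Under an either-outcome reading at 12 weeks, the family-wise error is about 8% to 10% rather than 5%. This rests on two-sided 5% tests, which are inferred, and on outcome correlations of 0.7 to 0, which are assumed. Under a both-outcomes reading the error is controlled, and the problem becomes power below that for pain alone. The 5% is therefore not assured; it is not shown to be breached. Naming 12 weeks limits the confirmatory question to two tests, but the primary label on weeks 26 and 52 and the 52-week aim should be brought into line with it.

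**What to change.** Before outcome data are examined by allocated group, amend the protocol wording as follows, and carry it into the analysis plan:

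- Make 12 weeks the only confirmatory time point.
- List pain and function at 26 and 52 weeks as secondary, reported with 95% confidence intervals and without a confirmatory claim.
- Reword the aim in the abstract and Discussion to match the 12-week primary time point.
- State a 12-week rule that holds 5% overall. One option is a fixed sequence: pain, on which the trial is sized, at two-sided 5%, then ODI at two-sided 5% only if pain is significant. The alternative is to require both at two-sided 5% and restate the joint power.

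The fixed sequence needs no change in sample size. Its price is that a result on ODI alone is supportive only, which the investigators should weigh against their view that both outcomes matter clinically. If they prefer to require both, error is controlled without an alpha split, but the power statement for pain no longer describes the trial's chance of success.

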#### Primary outcome measurements

Pain will be assessed using the numeric pain rating scale which is an 11-point scale from zero to ten with zero being ‘no pain’ and 10 ‘the most intense pain imaginable’ [29]. Participants select a value that is most in line with the intensity of pain that they have experienced in the last 24 h. The minimal clinically important difference has been demonstrated to be two out of 10 points [29].

Function will be assessed using the Oswestry Disability Index which consists of ten sections related to activities of daily living commonly affected by LBP [54]. Each section is scored from zero to five with the sum of the scores presented as a percentage. Higher values indicate a more severe impact of LBP on daily living. The minimal clinically important difference has been reported to be 12.88 [55].

### Secondary outcomes

The secondary outcomes will include:(i)Gluteus medius muscle activity from baseline to 12 weeks follow-up;(ii)Transversus abdominis muscle thickness from baseline to 12 weeks follow-up;(iii)correlation between foot type and change in pain and function;(iv)physical activity from baseline to 12, 26, and 52 weeks follow-up;(v)number of hours per day and week the prefabricated orthotic is worn over 12 weeks; and(vi)self-reported adverse events associated with the interventions over 52 weeks.

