**Methods:**

This study is a participant and assessor blinded, parallel-group, superiority randomised (1:1) controlled trial. The study will recruit 60 participants aged 18 to 65 years with chronic nonspecific low back pain. Participants will undergo randomisation to a control group (The Back Book) or an intervention group (prefabricated foot orthoses and The Back Book). The primary outcome measures will be change in pain and function from baseline to 12 (primary time point), 26, and 52 weeks. Secondary outcome measures include: gluteus medius muscle activity and transversus abdominis muscle thickness from baseline to 12 weeks, physical activity over 12, 26, and 52 weeks, and correlation between foot type and change in measures of pain and function. Number of hours per day and week that the prefabricated orthoses are worn, as well as, adverse events will be self-reported by participants. Data will be analysed using the intention-to-treat principle.

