An alternative mechanism of action of foot orthoses is by influencing muscle activity, with some research demonstrating that this is the case when walking and running [23]. This includes changes to timing and intensity of contraction of muscles of the lower leg and thigh [24], and the superficial muscles of the lower back [25]. However, it is unclear how foot orthoses may have this effect and whether or not it is beneficial [23]. Nevertheless, the potential for proximal muscle activity to be altered with the use of foot orthoses may be significant in the treatment of chronic nonspecific LBP, as this condition is associated with dysfunction of deep trunk muscles such as the transversus abdominis [26], and weakness of hip muscles including gluteus medius [27].

Current evidence regarding the efficacy of foot orthoses for treatment of chronic nonspecific LBP, particularly in the long term, is inconclusive, as is the potential effect of foot orthoses on more proximal hip and trunk muscle function. This randomised controlled trial aims to investigate the effectiveness of prefabricated foot orthoses compared to a placebo intervention on pain and function in people with chronic nonspecific LBP after 12, 26, and 52 weeks. The secondary aims include determining the effect that these interventions have on participants’ gluteus medius muscle activity and transversus abdominis muscle thickness over 12 weeks, and physical activity over 12, 26 and 52 weeks. Additionally, the effectiveness of the interventions on pain and function per foot type (supinated, neutral, or pronated), as well as, intervention adherence and adverse events will also be investigated.

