#### Secondary outcome measurements

Gluteus medius muscle activity, transversus abdominis muscle thickness and foot type will be assessed as outlined in Table 1. Physical activity will be assessed using the IPAQ-7 which consists of seven questions about the amount and intensity of moderate and vigorous physical activity undertaken in the past 7 days, as well as, the amount of time spent sitting [56]. The diary provided to participants in the prefabricated foot orthotic group will be used by participants to record the number of hours per day they have worn the orthotic device over 12 weeks. In addition to participants being able to contact the researchers at any stage of the trial to report adverse events, they will be asked if such events have occurred at the face to face follow-up session at 12 weeks.

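### Secondary outcome (vi) counts only adverse events associated with the interventions, so its arm counts cannot give an unbiased comparison of harm, and the wording conflicts with the rest of the article

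*Protocol article*

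**What the plan says.** Under Secondary outcomes, item (vi) of the protocol article is "self-reported adverse events associated with the interventions over 52 weeks". Read literally, association with an intervention is a condition for being counted.

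Four other places carry no such condition:

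- Abstract, Methods: "adverse events will be self-reported by participants".
- Background, closing aims: "intervention adherence and adverse events will also be investigated".
- Follow-up sessions: contact details are supplied "so participants can report adverse events at any stage of the trial".
- Secondary outcome measurements: besides spontaneous reports, "they will be asked if such events have occurred at the face to face follow-up session at 12 weeks".

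Neither route of collection is restricted to one arm. The article does not say who judges association or by what rule.

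On the interventions: "Participants in the control group will receive ‘The Back Book’ educational booklet". The other arm receives the same booklet plus prefabricated orthoses, to be worn for one year from baseline. The Participants section adds that, once randomised, each person receives a further information statement specific to the assigned intervention. Statistical and data analysis describes no between-arm test of adverse events.

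**The concern.** The control arm in a randomised trial supplies the background rate of complaints. New foot, knee or hip pain, or a fall, will occur in some participants whatever they are given. If every event counts in both arms, randomisation balances that background and the difference between arms estimates harm.

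A relatedness condition disturbs that balance when one arm wears a device and the other has read a booklet. The same new knee pain is easily linked to an insert and much less easily to a booklet, so more background events are removed from the control count. The filter can also err the other way. A real effect on the hip or knee may not be linked to something worn in the shoe, and would then drop out of the orthosis count. The Background proposes altered hip and trunk muscle activity as a possible mechanism, so effects away from the foot are relevant here.

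Adverse events are a stated secondary aim, and the Discussion supports the choice of device partly by the few adverse events reported in earlier research. Arm counts under the definition in (vi) would be a poor test of that premise. This point concerns which events count, not when participants are asked.

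**Working it through.** **The plan's own figures.** The article gives no adverse-event rate, attribution rate or adverse-event power, so there is no such figure to reproduce. Only the arm size is needed. Sample size gives 30 per group, and this reproduces: a 2-point difference with SD 2.5, 80% power and two-sided 5% needs 25 per group by the normal approximation, and 25 × 1.2 = 30.

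**Model.** Expected recorded risk in an arm = true risk of an adverse event × probability that the event is attributed to that arm's intervention. All risks and attribution shares below are assumptions.

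**Equal true risk in both arms, so the correct difference is zero.** Attribution in the orthosis arm is set at 50%. The last column is the exact probability that a two-sided Fisher test at 30 v 30 gives p < 0.05.

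| True risk, both arms | Booklet attribution | Recorded, orthoses | Recorded, booklet | Spurious excess (points) | P(Fisher p < 0.05) |
|---|---|---|---|---|---|
| 30% | 25% | 0.30 × 0.50 = 15% | 0.30 × 0.25 = 7.5% | 7.5 | 0.05 |
| 30% | 5% | 15% | 1.5% | 13.5 | 0.21 |
| 30% | 0% | 15% | 0% | 15 | 0.29 |
| 50% | 25% | 0.50 × 0.50 = 25% | 0.50 × 0.25 = 12.5% | 12.5 | 0.14 |
| 50% | 5% | 25% | 2.5% | 22.5 | 0.60 |
| 50% | 0% | 25% | 0% | 25 | 0.80 |

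**Reference cases.** If every event counts, the expected difference is 0 and the rejection probability is 0.026 (30% risk) or 0.027 (50% risk). If 50% of events are attributed in both arms, the expected difference is again 0. The spurious excess therefore comes from unequal attribution, not from filtering as such.

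**A true excess is also distorted.** Take true risks of 50% v 30%, a difference of 20 points:

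- 50% attribution in both arms: 25% − 15% = 10 points recorded.
- 50% and 25%: 25% − 7.5% = 17.5 points.
- 50% and 0%: 25% − 0% = 25 points.

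The filtered difference can fall on either side of the truth.

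**How near zero the control count would be.** At 30% true risk, the chance of no recorded control event among 30 is (1 − 0.075)^30 = 0.10 with 25% booklet attribution, and (1 − 0.015)^30 = 0.64 with 5%.

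**The case against.** The strongest case against the point is that one list item is being treated as a settled counting rule. Four other places speak simply of adverse events, both arms can report at any stage, and the 12-week question has no arm restriction. In that sentence the events asked about are most naturally adverse events in general. Unfiltered data from both arms may therefore be collected. No between-arm test is planned, every input above is assumed, and a condensed article may leave detailed definitions and form wording to a fuller document.

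Much of this stands, and it rules out several stronger readings that a reader might infer:

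- *The participant's own judgement decides what counts.* The events are self-reported, but no section says who judges association.
- *The booklet arm is bound to record almost nothing.* This needs very low booklet attribution, for which the article gives no figure. The booklet contains techniques for dealing with back pain, so a symptom could be linked to following it, and both arms receive it.
- *The control background rate is lost.* The collection sections do not establish that.
- *Worsening back pain would go unseen.* Pain and disability are the primary outcomes, scheduled for both arms at 12, 26 and 52 weeks without any attribution condition.
- *The outcome can say nothing about harm.* Device-attributed events remain a legitimate description of tolerability in the orthosis arm.

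The objection does not remove the definition itself. Item (vi) is the written definition of a named outcome. If collection is unfiltered, the definition contradicts it. If collection follows the definition, the arm counts are not comparable. Either way the text needs an edit. Nor does the absence of a planned test settle the matter, because counts reported side by side invite the same comparison.

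**Conclusion.** The point holds in a limited form. As worded, outcome (vi) makes association a condition for counting and disagrees with four other places in the article. With a worn device in one arm and only a booklet in the other, counts filtered this way cannot give an unbiased between-arm comparison of harm, chiefly for complaints outside the back.

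The direction rests on one judgement: that events are attributed more readily to a device than to a booklet. The size rests wholly on assumed inputs. The excess of about 7.5 to 25 percentage points needs equal true risks of 30% to 50%, 50% attribution to orthoses and 0% to 25% to the booklet. With equal attribution there would be no spurious excess. The rejection probabilities illustrate scale only. The primary analysis is unaffected.

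**What to change.** Reword outcome (vi) as all new or worsened adverse events since baseline in both arms, whatever the suspected cause. Ask about them with the same question in both arms and report them by arm. Record relatedness as a separate field, completed by a stated assessor, that does not decide whether an event is counted. Device-attributed events can then still be described as a subset. Bring the Abstract, Background, Follow-up sessions and Secondary outcome measurements into line with the new wording.

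The cost is one revised definition, one common question and one extra field. The small downside is more unrelated background complaints to record and tabulate. Finer detail, such as body-region checklists, can stay in the full protocol or case report form.
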